### Measures

The evaluation protocol is administered by therapists in a paper and pencil format at the participant’s health center in 5 different times: baseline, post-treatment, and follow-ups at 3, 6, and 12 months. To minimize biases, every administration of the diagnostic interview is done by two different psychologists, one face-to-face and the other by phone. Inter-rater reliability will be calculated. Assessment instruments include demographic characteristics (age, sex, education, marital status, and work status), a diagnostic interview, and well-established questionnaires for both primary and secondary outcomes.

### Primary outcomes

Severity of depression and anxiety symptoms are assessed with the Beck Depression Inventory (BDI-II) [23, 24] and the Beck Anxiety Inventory (BAI) [25, 26], respectively.

In addition to symptoms, a current diagnosis of anxiety and/or mood disorder is made with the lifetime version of the Anxiety Disorders Interview Schedule for DSM-IV (ADIS-IV-L) [4, 29]. The ADIS-IV-L is a semi-structured interview based on the diagnostic criteria of the Diagnostic and Statistical Manual of Mental Disorders -4th ed. (DSM-IV-TR) [4]. We have not used the ADIS-5 because it is not available in Spanish yet.

### Secondary outcomes

We administer the Overall Depression Severity and Impairment Scale (ODSIS) [30] and the Overall Anxiety Severity and Impairment Scale (OASIS) [31] weekly to assess the severity of depressive and anxiety symptoms, respectively. These measures are included to complement the results obtained with the BDI-II and the BAI, as well as to obtain a continuous assessment. The Positive and Negative Affect Scale (PANAS) [32, 33] is administered to evaluate positive and negative affect. The perception of control over anxiety is assessed by means of the Anxiety Control Questionnaire-Revised (ACQ-R) [34, 35]. Personality is measured with the NEO Five-Factor Inventory (NEO-FFI) [36], which offers a rapid and general measure of the Big Five personality traits: Neuroticism, Extraversion, Openness to experience, Agreeableness, and Conscientiousness. The Quality of Life Index (QLI) [37] is used to evaluate several aspects of health-related quality of life (i.e., physical disability, emotional well-being, self-care and independent functioning, occupational functioning, interpersonal functioning, social emotional support, community and services support, personal fulfillment, spiritual fulfillment, and overall quality of life). Similarly, the Maladjustment Inventory (MI) [38] is used to evaluate the extent to which the subject’s current problems impact negatively on different areas of daily life, namely, work, social life, leisure time, relationship with the partner, family life, and overall adjustment in daily activities. Additionally, we created an ad hoc questionnaire, the Treatment Opinion Scale (OTS), which is administered to participants in both conditions. Our ad hoc questionnaire evaluates the quality of the intervention (i.e., “How would you rate the quality of the treatment program you have received?”) and that of its components (i.e., “Have the techniques and exercises that we have practiced helped you regulate your emotions properly?”). Also, it measures the amount of discomfort experienced during treatment (i.e., “To what extent has this treatment caused you discomfort?”) and the experience of participating in a group format (i.e., “If you were to seek help again, would you choose a group treatment program?”). Some questions in the OTS use a4-point Likert scale (0 = “*poor”* or “*nothing”* to 3 = “*excellent”* or “*very much”*), while an 11-point response scale is selected in some items (0 = “*nothing”* to 10 = “*very much”*).

All measures used in the study have been standardized in Spanish. Administration time is between 90 and120 minutes for the ADIS-IV-L and approximately 90 min for the primary and secondary outcomes altogether.

### Analyses

First, we will calculate between-group differences in baseline measures, to ensure that randomization resulted in comparable groups. When normally distributed, continuous data will be analyzed via *t* test. If the Kolmogorov-Smirnov test indicates a non-normal distribution, a Mann-Whitney *U* test will be preferred. A chi-square test will be performed for categorical data. Then, to compare the efficacy of treatments, we will use a mixed-effects regression modeling with full information maximum likely hood estimation. This method is recommended over repeated-measures ANOVAs due to its flexibility in handling missing data [39]. Group (TAU or UP) will be used as the between-subject factor and time (baseline, post-treatment, and follow-ups) as the within-subject factor. Standardized effect sizes (Cohen’s *d*) will be calculated both for within and between-group analyses. Covariates will be demographic and clinical variables that are not comparable between groups, as exposed in the beginning of this section. Effect estimators in the UP group will be adjusted to control for the impact of group dependencies (i.e., homogenization of response to treatment due to shared environment), following the recommendations of Baldwin et al. [40].

To address problems of missing data or premature dropouts, an intention-to-treat analysis will be used and the most recent data will be imputed (last observation carried forward approach). This analytic strategy will only be performed with patients attending at least 50% of sessions, as recommended in past research [41], and with those responding to at least one of the post-treatment assessments (i.e., end of treatment or follow-ups) so that treatment effect may be captured by the last observation. In addition to the last observation forward, missing data in the UP group will also be replaced with the CBT mean +/− the non-inferiority margin and missing data in the CBT group will be replaced with the UP mean (i.e., bias toward inferiority) [42]. Results using a last observation carried forward approach and a bias toward inferiority imputation will be compared against a completers-only strategy and all of them will be reported. To ensure non-inferiority, a per-protocol analysis will also be conducted. Following FDA guidelines [16], non-inferiority will be concluded if the upper bound of the 95% CI for the effect estimate in the UP condition is smaller than the non-inferiority margin (50% of the effect estimate of individual CBT when compared to placebo). Due to the non-inferiority design (i.e., the Unified Protocol in a group format is not worse than individual CBT), a one-sided confidence interval will be used in the analyses. A post-hoc power analysis with the primary outcomes will be conducted at post-treatment and follow-ups using the sample size and obtained effect size.

The researcher analyzing data, [name], will be blind to arm allocation. To ensure that, arms will be given arbitrary letters (A and B) in the database and only the lead researcher, [name], will know the correspondence between study allocation arms and assigned arbitrary letters.

Reporting of results will follow the Consolidated Standards of Reporting Trials (CONSORT) recommendations [43].

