### Sample size

To calculate the sample size required, the non-inferiority margin (i.e., tolerable amount of effect difference between TAU and the UP) has to be set. This was done according to the US Food and Drug Administration (FAD) [16] guidelines. First, the effect of the active control (i.e., CBT) compared with placebo needs to be established, based on previous research. Meta-analyses indicate medium-to-large effect sizes (between .4 and .8) of individual CBT on EDs [17–19]. Then, an amount of minimum preserved effect needs to be set. According to FDA guidelines, a preserved effect of a 50% of the effect of the active control (individual CBT) is recommended, so this was set to .3 in the present study. Because, to the best of our knowledge, no meta-analysis has reported effect sizes for each outcome included in the study, the margin has been defined according to the pooled estimate of overall effectiveness of CBT.

With regards to treatment satisfaction, a 35% non-inferiority margin was established. This is based on a meta-analysis of computer CBT, in which between 70% and 100% of depressed patients were satisfied with treatment [20]. To the best of our knowledge, there is no meta-analysis of treatment satisfaction with individual, face-to-face CBT and its study is rare. However, similar to group UP, computer CBT has been argued to be an alternative to traditional CBT [20], especially when resources are limited, so the aforementioned satisfaction rates of computer CBT might be relevant in the present study.

We obtained a sample size of 95 participants for each group with 80% power, an alpha level of .05 (one-sided), a standard deviation of .83 in the CBT group compared with placebo, and a non-inferiority limit of .30 [21, 22]. Considering a drop-out of 15%, we decided to recruit 110 subjects in each group. When registering the study, a sample size of 200 individuals was calculated. However, this was increased by 20 patients after considering non-inferiority sample size calculations.

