### Procedure

Randomization has been performed by a researcher unrelated to the study using a computer-generated sequence (Randomizer). In the program, the researcher generated 1 set of numbers with 220 numbers, which had a 1-to-2 range. Randomization is stratified according to the severity of the primary measures of depression (BDI-II) [23, 24] and anxiety (BAI) [25, 26], using the recommended cut-off in manuals. In the BDI-II, these are 0–13 for normal, 14–19 for mild, 20–28 for moderate, and for 29–63: severe depressive symptoms [24]. As for anxiety symptoms (BAI), cut-off are 0–7 for normal, 10–18 for mild, 16–25 for moderate, and 26–63 for severe [26]. Stratification is made to ensure a comparable proportion of severely depressed and anxious individuals in each group. For each subgroup (i.e., severe or less severe depression and/or anxiety), participants are randomly assigned to the UP or to TAU. In the UP condition, there are between 8 and 10 participants and 2 clinicians (therapist and co-therapist) per group. In the TAU condition, participants receive individual sessions with one therapist.

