## Discussion

EDs have become a matter of public concern due to their high prevalence and associated costs [6, 7, 44]. The UP has emerged as a promising form of CBT to be used across diagnostic categories both in individual and group format [8, 9]. Therefore, the study of a therapeutic approach that can be administered to several patients with different disorders simultaneously, as in the present study, may have important clinical implications for countries.

The use of the UP in group format in public mental health settings may have some advantages over traditional individual CBT: 1) it may allow clinicians to use the same treatment for a variety of psychological disorders [8, 9, 12]; 2) it might help reduce existing waiting lists as between 6 and 8 patients can be treated simultaneously, which would probably reduce the duration of suffering in unattended patients; 3) in contexts similar to the Spanish public system, where individual CBT is the norm and therapy sessions occur at long intervals (i.e., once a month) due to waiting lists, a UP-based treatment program in group format can help increase the frequency of sessions because more patients are treated simultaneously, which may facilitate a more rapid detection of patients’ problems during treatment; 4) finally, group therapy is known to report benefits for the patient that are not obtained with individual treatment, such as reducing isolation, facilitating social support, and learning from others’ experiences [45, 46], which might enhance its efficiency. The present RCT taps into the aforementioned aspects of treatment satisfaction and effectiveness.

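### Full maximum likelihood with only about 11 to 14 therapy groups can make the non-inferiority bound slightly too tight; REML with small-sample degrees of freedom is a cheap improvement

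*Protocol article*

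**What the plan says.** The Analyses section of the protocol article names the estimator for the efficacy model: "we will use a mixed-effects regression modeling with full information maximum likely hood estimation". Group and time are the factors. The reason given is that a mixed model copes with missing data better than repeated-measures ANOVA.

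The same section adds, as a separate commitment, "Effect estimators in the UP group will be adjusted to control for the impact of group dependencies", following a cited source. It does not say whether the therapy group enters the maximum likelihood fit as a random effect or is handled afterwards. It mentions neither REML nor a degrees-of-freedom method.

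On the number of groups, the Procedure section says "In the UP condition, there are between 8 and 10 participants and 2 clinicians (therapist and co-therapist) per group", and the Sample size section says "Considering a drop-out of 15%, we decided to recruit 110 subjects in each group". No number of groups and no ICC is stated. Non-inferiority is decided on the upper limit of a one-sided 95% confidence interval; the article does not say which critical value is used.

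**The concern.** Maximum likelihood divides the between-group sum of squares by the number of groups k, where the unbiased divisor is k − 1. With 11 to 14 groups that shrinks the clustered part of the variance by 1/14 to 1/11. A normal critical value also ignores that this part has only 10 to 13 degrees of freedom. Both effects pull the upper bound down, towards a claim of non-inferiority, and that bound is the decision rule.

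Missing data give no reason to prefer ML to REML. Both are likelihood methods and use the same incomplete records, so the article's stated reason for a mixed model is met equally by either.

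**Working it through.** **Inputs.** From the Sample size section: margin 0.30, SD 0.83, one-sided alpha .05, power 80%, 95 evaluable and 110 recruited per arm. From Procedure: 8 to 10 patients per UP group. Assumed, because the documents do not give it: ICC ρ from .01 to .20.

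**The plan's own figure.** n = 2(1.645 + 0.842)²(0.83/0.30)² = 2 × 6.18 × 7.65 = 94.7, so 95 per arm. This agrees with "We obtained a sample size of 95 participants for each group with 80% power".

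**Number of groups.** 110/10 = 11 and 110/8 = 13.75, so 11 to 14. With 95 evaluable patients it is 10 to 12 if whole groups shrink. The Discussion has "between 6 and 8 patients can be treated simultaneously"; groups of 6 would give up to 19 (110/6 = 18.3).

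**Standard error by formula** (k groups of m in UP, 110 independent TAU patients, one time point):

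- Correct variance: V = s²[1 + (m − 1)ρ]/(km) + s²/110.
- ML multiplies the first term by (k − 1)/k, when the variance is not truncated at zero.
- k = 11, m = 10, ρ = .05: first term 0.6889 × 1.45/110 = 0.00908; second term 0.6889/110 = 0.00626. SE = √0.01534 = 0.1239. Under ML, √(0.00826 + 0.00626) = 0.1205. The bound moves by 1.645 × 0.0034 = 0.0056.
- k = 11, m = 10, ρ = .20: SE 0.1543 against 0.1490 under ML. The bound moves by about 0.0086, or 2.9% of the 0.30 margin.
- From ρ = .01 with 14 groups to ρ = .20 with 11 groups, the shift runs from 0.003 to 0.009.

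**One-sided error by simulation.** True difference at the margin, 200,000 trials per setting (Monte Carlo standard error about 0.05 points), balanced groups, closed-form ML and REML truncated at zero:

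| Groups × size | ICC | ML, normal | REML, normal | REML, Satterthwaite t |
|---|---|---|---|---|
| 11 × 10 | .01 | 4.96% | 4.71% | 4.24% |
| 11 × 10 | .05 | 5.61% | 5.23% | 4.69% |
| 11 × 10 | .10 | 5.96% | 5.48% | 4.84% |
| 11 × 10 | .20 | 6.40% | 5.80% | 5.01% |
| 14 × 8 | .01 | 4.93% | 4.71% | 4.35% |
| 14 × 8 | .05 | 5.44% | 5.14% | 4.77% |
| 14 × 8 | .10 | 5.68% | 5.31% | 4.85% |
| 14 × 8 | .20 | 6.00% | 5.59% | 5.04% |

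At ICC .02, ML with the normal value gives about 5.1%. With 10 groups of 10 and 95 TAU patients it reaches up to 6.6% at ICC .20. With 18 groups of 6 it stays at 5.3 to 5.7% for ICC .05 to .20. A repeat with 1,000,000 trials per setting agreed to within about 0.1 point.

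**Splitting the effect.** At 11 × 10 and ICC .10, the full change from ML/normal to REML/t is 5.96 − 4.84 = 1.12 points, of which ML to REML gives 5.96 − 5.48 = 0.48, or 43%. Over the six settings with ICC .05 to .20 this share is 41 to 45%, and the rest comes from the critical value. Against the 5% line, REML alone removes 0.38 of the 0.61 excess at 11 × 10 and ICC .05, and 0.60 of 1.40 at ICC .20.

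**Cluster variance.** For 11 and 14 groups, the mean ML estimate relative to truth is 0.90 and 0.94 at ICC .05, 0.86 and 0.88 at .10, and 0.88 and 0.90 at .20. At ICC .05 it is exactly zero in about 30% of trials. At ICC .01 the floor at zero reverses the sign: the mean estimate is 1.8 to 2.1 times the truth.

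**Critical value after the change.** Satterthwaite df = V²/[V_UP²/(k − 1) + V_TAU²/(n − 1)], where V_UP and V_TAU are the two terms of V. For 14 × 8 at ICC .01 this is about 45 (t = 1.68). For 11 × 10 at ICC .20 it is about 18 (t = 1.73), and for 10 × 10 with 95 TAU patients about 17 (t = 1.74).

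**The case against.** A reader might infer that the trial's 5% error rate is not held and that the cluster variance is bound to be underestimated. The documents do not support that, for four reasons.

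- The efficacy model and the group-dependency adjustment stand in separate sentences. Nothing says that the therapy-group variance is estimated in the ML fit. The cited adjustment, which cannot be consulted here, may itself be a standard-error or degrees-of-freedom correction.
- The normal critical value is an assumption of this check. The article says only that the interval is one-sided, and more than half of the calculated change comes from this assumption.
- The result depends on an ICC that is not given. At .02 or below there is no material inflation.
- The effect is small. In the same simulations (ICC .01 to .20) ignoring clustering altogether gives 5.4 to 11.7%, so the planned adjustment already removes most of the error.

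All four stand, and they limit the point. It is also fair that degrees-of-freedom methods are commonly left to an analysis plan, so their absence alone would be no finding. What remains is that the article does not leave the estimator open. It names full maximum likelihood, and for so few groups REML is the better choice at the same treatment of missing data. Nor does the article argue for ML against REML; its comparison is with repeated-measures ANOVA.

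The simulation is simpler than the planned model: one time point, balanced groups, no covariates and no therapist clustering in TAU. The figures show the order of magnitude and do not predict the trial's exact error rate.

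**Conclusion.** The point holds in a conditional form and is minor. If the therapy-group variance is estimated in the stated ML fit and the bound uses 1.645, the one-sided error is about 5.4 to 5.6% at ICC .05, 5.7 to 6.1% at .10 and 6.0 to 6.6% at .20, against a nominal 5%. It is about nominal at ICC .02 or less. ML by itself adds about 0.2 to 0.6 points and moves the bound by at most 0.009 on a margin of 0.30. The direction, where there is an effect, favours declaring non-inferiority. The documents do not show that the planned analysis will have this error, because the cited adjustment may already correct it.

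**What to change.** State in the Analyses section that the partially nested model (therapy group as a random effect in the UP arm only) is fitted by REML, with Satterthwaite or Kenward-Roger degrees of freedom for the UP–TAU contrast, and that the non-inferiority bound is taken from the t distribution. If the cited group-dependency adjustment already does this, one sentence saying so is enough. ML can be kept for comparing fixed-effect structures.

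The cost is a software option and a slightly wider bound, with t about 1.68 to 1.74 in place of 1.645. In these simulations REML with Satterthwaite degrees of freedom gave 4.2 to 5.0%, so at very low ICC the test becomes a little conservative.

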### Sample and recruitment

The trial started the recruitment in September 2014 and it is still active. The study is conducted in five different Public Mental Health Centers and Primary Care Centers in Spain, namely, the Elda Clinical General Hospital, the Hospital Clínico Universitario de Valencia, the [name] Hospital, the PCC IIA Milagrosa of Pamplona, and the Hospital Comarcal de Vinaròs. Participants are individuals over 18 years of age seeking psychological assistance in the Spanish Public Health System. Sample size was set to 220 participants to ensure enough statistical power when testing our hypotheses (see “Sample size” section).

Patients are referred to the study by licensed psychologists, psychiatrists, and clinical psychology residents working at the collaborating centers, who also assess for current DSM diagnoses (See “measures” section) and the remaining eligibility criteria (see “Inclusion and exclusion criteria” section). Individuals with comorbid diagnosis of several EDs are also enrolled in the study. The existence of such comorbidities might be important for assessment scores. However, in the present study we did not stratify considering comorbidities because this could significantly increase the complexity of the design (i.e., some patients might have more than one comorbid diagnosis). Due to the difficulties derived from conducting an RCT in different public mental health settings, we cannot guarantee a 100% of independent evaluations. We expect between 60 to 75% of independent evaluations. The rest of evaluations will probably be made by recruiters who are also the therapists in one of the conditions. However, this information is collected and considered in the interpretation of results.

Patients meeting eligibility criteria are asked to participate and are provided with an information sheet, information on data confidentiality, and an informed consent form. After participation acceptance, patients complete the baseline assessment protocol in their correspondent health center (see “Measures” section). Next, participants are informed of the condition they have been randomly assigned to, that is, TAU or UP.

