Enrollment period and waiting time are comparable across participants (2–3 weeks). When the time from assessment, diagnosis, and randomization to the onset of the intervention takes more than 2 weeks we establish a new period of assessment. For ethical reasons, if a patient feels uncomfortable with the group format at any time during the study, he/she is allowed to join the TAU condition. This information is collected and considered in the analyses.

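### Covariates are selected by baseline significance tests and baseline enters only as a level of time, so the stratified baseline BDI-II and BAI scores will seldom be adjusted for and the interval is wider than it needs to be

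*Protocol article*

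**What the plan says.** The Analyses section begins with baseline comparisons: "First, we will calculate between-group differences in baseline measures, to ensure that randomization resulted in comparable groups". These use a t test, a Mann-Whitney test or a chi-square test, depending on the variable. The efficacy model is a mixed-effects regression, described as follows: "Group (TAU or UP) will be used as the between-subject factor and time (baseline, post-treatment, and follow-ups) as the within-subject factor". The covariate rule comes next: "Covariates will be demographic and clinical variables that are not comparable between groups", with a reference back to those baseline comparisons. The section also plans an adjustment for dependency among patients treated in the same UP group.

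Two other sections bear on this. Procedure states that "Randomization is stratified according to the severity of the primary measures of depression (BDI-II", and the same sentence adds anxiety on the BAI. Both are primary outcomes. The TAU section names one further covariate, number of sessions, whatever the baseline balance. The article names neither the baseline scores, nor the severity strata, nor centre as a prespecified model term.

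**The concern.** In a randomised trial a baseline test detects only chance differences. A covariate is worth including because it predicts the outcome, not because it happened to differ between arms. Selecting by test leaves the primary model unknown until the baseline data have been examined.

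Here the rule also works against the design. Stratification balances BDI-II and BAI severity, so the variables most likely to predict post-treatment BDI-II and BAI are the ones least likely to be flagged. The analysis then ignores a balance that the design went to some trouble to create, and the standard error is too large.

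Having baseline in the response does not recover the loss unless baseline means are held equal across arms. Without that constraint, the natural group-by-time contrast is a difference in change scores. Because non-inferiority is decided on a confidence bound, an unnecessarily wide interval translates directly into lost power.

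**Working it through.** **Inputs.** From Sample size: 95 evaluable per arm, 80% power, one-sided alpha 0.05, SD 0.83, margin 0.30. Assumed: a true difference of zero; 0.83 is the SD of a single post-treatment score; baseline and outcome have equal SDs and correlation rho. The documents give no rho, so a range is shown.

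**The plan's own figure.** n per arm = 2 × [0.83 × (1.645 + 0.842) / 0.30]² = 94.65, rounded up to 95. The stated figure reproduces, and it rests on an unadjusted SD.

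**Variance per patient, with s = 0.83.**
- Unconstrained difference in change: 2s²(1 − rho).
- Baseline as covariate, or baseline means constrained equal: s²(1 − rho²).
- Ratio, change to adjusted: 2(1 − rho) / (1 − rho²) = 2/(1 + rho), which exceeds 1 for every rho below 1.

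**Power at 95 per arm** = Φ(0.30 / [SD × √(2/95)] − 1.645), where SD is the square root of the variance above. For rho = 0.5 the change SD is 0.83 × √1 = 0.83, the standard error is 0.1204, and power is Φ(2.491 − 1.645) = 80.1%. The adjusted SD is 0.83 × √0.75 = 0.719, the standard error is 0.1043, and power is Φ(2.876 − 1.645) = 89.1%.

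| Assumed rho | Variance ratio 2/(1+rho) | Power, change contrast | Power, baseline-adjusted | n per arm for 80%: change vs adjusted |
|---|---|---|---|---|
| 0.4 | 1.43 | 73.5% | 85.8% | 114 vs 80 |
| 0.5 | 1.33 | 80.1% | 89.1% | 95 vs 71 |
| 0.6 | 1.25 | 87.3% | 92.9% | 76 vs 61 |

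The change contrast falls short of 80% only when 2(1 − rho) exceeds 1, that is, when rho is below about 0.5.

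**Simulation of the selection rule.** 190 patients, one baseline score, allocation balanced within four severity strata, 2,500 runs per setting. Test-selected means adjusting for baseline only if its t test gives p < 0.05. Type I error is evaluated at a true difference equal to the margin; nominal is 0.05.

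| rho = 0.5, stratified | Type I error | Power |
|---|---|---|
| Unadjusted post-treatment comparison | 0.036 | 0.816 |
| Test-selected | 0.036 | 0.816 |
| Change contrast | 0.034 | 0.820 |
| Baseline-adjusted | 0.054 | 0.886 |
| Baseline-adjusted plus strata | 0.051 | 0.882 |

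The test-selected results equal the unadjusted ones, so the rule in effect never admitted the stratified score. The estimators' true spread was similar (SD 0.1077 unadjusted, 0.1066 change, 0.1049 adjusted, from the power runs). Under effective stratification the loss therefore comes mainly from an overstated standard error. At rho = 0.7 the unadjusted and test-selected analyses both gave type I error 0.016 and power 0.868, against 0.051 and 0.966 adjusted.

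Procedure also describes a single list of 220 numbers. If allocation was in effect unstratified, adjustment still helps: at rho = 0.5, power was 0.885 adjusted, 0.802 for the change contrast and 0.801 test-selected.

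**The case against.** The best defence is that baseline in the response vector is fully efficient if baseline means are constrained equal, and that such parameterisation is often left to an analysis plan. This stands in part. The article neither states nor excludes the constraint and does not name the decision contrast, so the change-score reading is an inference from the two factors listed. It does not rescue the covariate rule, which is stated outright.

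It is also true that no validity harm follows. The simulated error rates under the plan's approach are below nominal, so false non-inferiority is not made more likely. The gain shrinks as rho rises, and the formula does not cover diagnosis, the binary primary outcome.

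Some stronger readings are tempting but unsupported:
- **Covariates enter only through imbalance.** Number of sessions is named in the TAU section regardless of balance.
- **The trial is already under-powered.** The 95 per arm reproduces from its own inputs. A shortfall under the change contrast needs rho below about 0.5, which the documents do not establish.
- **A post-allocation score becomes the baseline.** Sample and recruitment says that when the interval to the start of the intervention "takes more than 2 weeks we establish a new period of assessment". It does not say that these scores replace the original ones, and it places the baseline assessment before patients learn their arm.
- **Omitting strata and centre is a major loss in itself.** Stratum terms added nothing beyond the continuous score (0.882 against 0.886). Centre is not a stated stratum, and its gain cannot be quantified from the documents.

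**Conclusion.** The point holds as a matter of prespecification and efficiency. The stated rule leaves the covariate set open until baseline data are seen, and under the planned stratification it will usually exclude the baseline BDI-II and BAI scores. The consequence is a conservative interval and lost power.

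For an unconstrained group-by-time contrast the loss is about 12, 9 and 6 percentage points of power at rho 0.4, 0.5 and 0.6. This rests on 0.83 being a single-score SD, a true difference of zero and the assumed correlations. It applies to the continuous primary outcomes before any allowance for therapy-group clustering. The direction does not depend on rho; the size does. The plan should be changed, but nothing here invalidates the stated sample size.

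**What to change.** Drop the baseline significance tests as the means of choosing covariates; a descriptive baseline table can stay. For BDI-II and BAI, prespecify a mixed model in one of two forms: the continuous pre-allocation baseline score as a covariate with its interaction with time, or baseline kept in the response with means constrained equal across arms. Keep the planned adjustment for UP-group dependency. Say explicitly that the pre-allocation score is the baseline.

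Severity-stratum terms and centre may be added as secondary terms. If stratum terms are used, the BAI bands in Procedure must first be reconciled, since they leave out scores 8–9 and overlap at 16–18. Whether number of sessions belongs in the model is a separate question that needs its own decision.

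The main change needs no new data, because the baseline scores are already collected. It costs a revision of the analysis text, made before the outcome data are examined.
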